**Figure 2 F2:**
[figure not shown]
STND Treatment Group Additional Exercise.

**Table 2 T2:** STND treatment group additional exercise

**Control subjects**	**Session 1-3**	**Session 4-6**	**Session 7-10**
Single Leg Balance	3 x 30 sec	3 x 45 sec	3 x 1 minute
(**Do Not** “progress” with unstable surfaces or ball toss or perturbation)	(Level Ground)	Add sham progression: (stabilize t-band with standing leg, complete hip flexion with tband around ankle)	same

The expertise of the treating therapists will determine if any task is unsafe for the patient and should be held from the protocol at any point. If a patient develops increased knee joint effusion [41] or additional complaints of pain, a clinical decision making protocol has been established as a guide for the therapists to determine how to modify the training program (Figure 3). If a patient present with a 2+ effusion at any point during the training program the training protocol will be held and the patient will be treated with effusion management including retrograde massage, ice and elevation. The patient will be educated on proper effusion management techniques such as keeping the knee wrapped with a donut and compression wrap (Figure 4), as well as icing several times a day with the leg elevated. At the following session if the effusion has decreased to a 1+ the training will resume at the same level of difficulty, if the patient has trace or no effusion then the training program will be progressed accordingly. Conversely, if the patient continues to demonstrate a 2+ effusion the training will be held, the patient will be treated accordingly for effusion and the research team will be notified. Additional complications that occur throughout training will be treated as needed by the treating therapist. If additional symptoms or impairments are limiting completion of the training program the principle investigator will be notified. If the patient cannot resume the training program for any reason the training will be terminated and post-training data will be collected. The patient will continue to be treated accordingly for their impairments.

**Figure 3 F3:**
[figure not shown]
ACL-SPORTS training effusion protocol.

**Figure 4 F4:**
[figure not shown]
Donut with compression wrap for effusion management.

### Outcomes measures

The primary outcome variables of interest for this study will include gait biomechanics, clinical outcome measures and knee joint loading.

Gait biomechanics will be assessed using a 3D motion capture system (VICON, Oxford Metrics Ltd., London, England) sampled at 120 Hz. Twenty static retro-reflective markers will be placed on the pelvis and lower extremities to identify limb segments. An embedded force plate (Bertec, Worthington, OH) will simultaneously collect kinetic data and used to determine timing variables during the gait cycle. Five walking trials will be collected for each limb while patients maintain a self-selected walking speed with ± 5% variability. These data will be post-processed using rigid body analysis and inverse dynamics with custom software programming (Visual3D, C-Motion, Inc., Germantown, MD, USA; LabVIEW 8.2, National Instruments Corp., Austin, TX, USA). Variables will be lowpass filtered at 6 Hz and 40 Hz. Initial contact and toe off will be determined using a 50 N force plate threshold. All walking trials will be normalized to 100% of stance before being averaged for statistical analysis. Hip and knee joint angles, moments and excursions will be evaluated between limbs in both the sagittal and frontal plane.

Clinical outcome measures will include quadriceps strength index, single-legged hop test measures and patient reported outcome measure. Quadriceps strength will be measured using a maximal voluntary isometric contraction (MVIC) with a burst superimposition technique [49]. Activation deficits and isometric quadriceps strength will be measured using an electromechanical dynamometer (KIN-COM, Chattanooga Corp., Chattanooga, TN). Patients will be seated in an upright position with the hip and knee flexed to 90 degrees. Testing will be completed on the uninvolved limb followed by the involved limb. A quadriceps index (QI) will be calculated as the quotient of the involved quadriceps MVIC to the uninvolved quadriceps MVIC multiplied by 100. The single-legged hop test measures [50] will consist of four hop tests in which each test will be administered as the uninvolved limb followed by the involved limb for the single hop for distance, crossover hop for distance, the triple hop for distance and 6-meter timed hop tests. A limb symmetry index (LSI) will be calculated from the average of two trials as the involved limb hop distance divided by the uninvolved limb hop distance multiplied by 100. The 6-meter timed hop will be calculated as the uninvolved limb hop time divided by the involved limb hop time multiplied by 100. Patient reported outcome measures will be completed after all objective clinical measures have been collected. The Knee Outcome Survey-Activities of Daily Living Score (KOS-ADLS) and the Global Rating Scale of Perceived Knee Function (GRS) will be used to determine the patients perceived knee function. A strict return to sport criteria, established by Fitzgerald et al. [38], requires the patient to achieve ≥ 90% on the following measures: QI, all 4 single-legged hop tests, KOS-ADL’s and GRS. Patients will be required to meet these criteria after training to allow for progressive return to sport activities. If patients do not meet these criteria after training they will be repeatedly tested every 2-4 weeks until all measures are met prior to returning to sport activity. The ACL-Return to Sport after Injury (ACL-RSI) has been validated to measure fear in patients after ACLR. This patient reported outcome measure will be used to objectively measure patient fear in the short to medium term (6 months -2 years).

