### Procedure

Once a patient has consented to be contacted by research staff, eligibility will be determined from patient chart review and patient dialogue. All testing measures will be performed at the University of Delaware Physical Therapy Clinic by the same assessor, blinded to group assignment. Enrolled study participants will complete initial baseline testing and 10 treatment sessions followed by post-training, 1 year and 2 year follow-up testing sessions. Testing will be completed no more than two weeks prior to initiation and two weeks after the completion of the 10 training sessions. Ethical approval has been obtained from the University of Delaware Human Subjects Review board. All participants will provide written informed consent to all research testing procedures.

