#### Joint loading

Electromyography (EMG)-driven musculoskeletal modeling will be used to estimate muscle forces from EMG muscle data during walking trials [51]. Anatomical modeling of the pelvis and lower limbs will be scaled initially for each subject. The model will then be calibrated based on muscle parameters used to determine the EMG-to-force relationship. Through iterative adjustments, the muscle parameters will result in strong agreement with the sagittal plane net moments calculated from forward and inverse dynamics. Once the ideal model is determined, the muscle forces will be predicted from mathematical calculations from recorded EMG for three walking trials and converted to muscle force. A frontal plane moment balancing algorithm [52] will be used to calculate medial and lateral compartment contact forces. The knee adduction moment will be calculated using inverse dynamics and will be expressed about each contact point in the medial and lateral compartments. A balance of contact forces and muscle forces at each contact point will be summated to express the contact forces in the each compartment as well as the total joint forces.

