### Data and statistical analysis

Differences between groups will be analyzed using an analysis of covariance (ANCOVA) for biomechanical gait measures and an analysis of variance (ANOVA) will be used for clinical variables. Group assignment will be blinded to the researcher using A and B variables. Assumptions of ANOVA testing will be confirmed prior to statistical analysis. Training group randomization will be used as the between-subjects factor with a within-subjects factor of time. A significance level of p < 0.05 will be set a priori.

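### Three whole outcome domains, at least 22 variables, are primary with no lead variable, visit or success rule, while the sample size rests on sagittal-plane gait alone

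*Protocol article*

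**What the plan says.** Under Outcomes measures the protocol article states: "The primary outcome variables of interest for this study will include gait biomechanics, clinical outcome measures and knee joint loading". The Abstract names the same three domains, and secondary outcomes have a section of their own, so the primary label is deliberate.

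The domains are then filled in:

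- **Gait:** "Hip and knee joint angles, moments and excursions will be evaluated between limbs in both the sagittal and frontal plane".
- **Clinical:** a quadriceps index (QI), four hop tests, and the KOS-ADLS and GRS questionnaires. The same seven form the return-to-sport criterion, which "requires the patient to achieve ≥ 90% on the following measures: QI, all 4 single-legged hop tests, KOS-ADL’s and GRS".
- **Joint loading:** medial and lateral compartment forces, "summated to express the contact forces in the each compartment as well as the total joint forces".

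Under Procedure, participants have baseline testing and "10 treatment sessions followed by post-training, 1 year and 2 year follow-up testing sessions". Under Data and statistical analysis the model is described as follows: "Training group randomization will be used as the between-subjects factor with a within-subjects factor of time". The error rate is given once: "A significance level of p < 0.05 will be set a priori".

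The Sample size section refers to clinically important differences for sagittal-plane gait variables, in the plural and without naming a joint. It gives 72 subjects at α = 0.05, β = 0.20 and an effect size of 0.3, raised to 80 for 10% dropout. The Hypotheses section lists four between-group claims and does not say whether one or all of them must hold.

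**The concern.** A 5% error rate and an 80% power statement mean something only when they attach to a defined claim. Here the primary claim is spread over three domains, and nothing in the article says which variable, at which visit, decides the trial. A report could follow the article faithfully and present whichever variable reached p < 0.05 as a primary result. A null trial could then be read as positive, and the reader could not tell how many chances it had.

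The sample size adds to this. It is argued from one part of one domain, so a negative result in the clinical or loading domain has no planned power behind it.

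**Working it through.** **The plan's own figure.** 72 / 0.90 = 80, so the dropout step is exact. The 72 can be reached if 0.3 is read as Cohen's f, that is d = 0.6:

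- A one-sided t-test at 0.05 needs 72 in total (power 0.809).
- A two-sided t-test needs 90, and at 72 its power is 0.71.
- Two-sided testing reaches 72 with a covariate correlation of about 0.45, or with a between-group test over two visits correlated at about 0.6. The article states neither correlation.
- Read as d = 0.3, a two-sided test needs 352.

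Under every reading the calculation concerns a single test on a gait variable.

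**Counting the primary variables** (minimum, one value per cell):

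- Gait: 2 joints × 3 quantities × 2 planes = 12
- Clinical: QI 1 + hop tests 4 + KOS-ADLS 1 + GRS 1 = 7
- Loading: medial, lateral, total = 3
- Sum: 12 + 7 + 3 = 22

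The ACL-RSI and the quadriceps activation deficit are described in the same clinical paragraph. Counting them gives 24.

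**Chance of at least one false positive**, with one group test per variable, each at two-sided 0.05, and no true effect:

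- Independent tests: 1 − 0.95^22 = 0.676.
- Expected number of false positives, whatever the correlation: 22 × 0.05 = 1.1.
- Common correlation ρ, with Φ and φ the standard normal distribution and density: 1 − ∫ [Φ((1.96 − √ρ·x)/√(1−ρ)) − Φ((−1.96 − √ρ·x)/√(1−ρ))]^22 φ(x) dx.

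| Assumed ρ | Chance of ≥ 1 false positive |
|---|---|
| 0 | 67.6% |
| 0.1 | 66.0% |
| 0.3 | 56.9% |
| 0.5 | 43.9% |
| 0.7 | 30.1% |

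The chance falls below 50% at ρ of about 0.41.

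A single common correlation is crude, so the 22 tests were also simulated in blocks of 12, 7 and 3. Correlations of 0.3 within and 0.1 between domains give 61%. The pair 0.5 and 0.2 gives 52%, 0.7 and 0.3 gives 41%, and 0.8 and 0.5 gives 32%.

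**For comparison**, one nominated variable per domain, still unadjusted, gives 1 − 0.95^3 = 14.3% if independent. A Bonferroni level over 22 tests would be 0.05 / 22 = 0.0023.

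**The case against.** **The analysis plan may deal with this.** A condensed article may leave the multiplicity method to a document not shown, and the article does not say in so many words that every variable is tested at 0.05 without adjustment. That stands, and the figures are therefore conditional. But the choice of primary outcome belongs in the protocol, and this article makes that choice: three domains, stated twice. An adjustment elsewhere would still leave no lead variable or visit here.

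**No rule says that one win is enough.** The hypotheses are listed jointly. If all had to hold, there would be no inflation of this kind. This is correct, and the article does not settle it. The error rate depends on a rule that is not given.

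**The variables are not weakly correlated.** Total joint force is summed from the compartment forces, the muscle model is tuned to the sagittal moments, and the four hop tests use the same pair of limbs. This stands. A reader might infer that a false-positive success is more likely than not, but that needs a common correlation below about 0.41, and the article gives no correlations. At 0.7 the chance is still six times the nominal 5%.

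**Analysts are blinded with A and B labels.** This limits selection in a favoured direction. It does not change how often some variable crosses a two-sided 0.05 by chance.

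Three stronger readings are not supported:

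- A reader might multiply 22 variables by three follow-up visits. Time is a within-subjects factor in the stated model, so 66 separate tests do not describe this plan.
- A reader might infer that retesting pushes later clinical scores to a common level in both arms, since athletes below the criteria "they will be repeatedly tested every 2-4 weeks until all measures are met prior to returning to sport activity". The rule applies only before return to sport, and the article gives no means or spreads from which to size an effect.
- A reader might add that two of the seven clinical measures are self-reports by unblinded patients. That is a separate question about bias and is no evidence on multiplicity.

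**Conclusion.** The point holds and should be fixed before the results are analysed. The article fixes a primary set of at least 22 variables with no lead variable, visit or success rule. The chance of at least one nominally significant primary result when there is no true effect then lies between 30% and 68%, for common correlations from 0.7 down to 0. This rests on three assumptions: each variable is tested once at two-sided 0.05, any one significant result may be presented as a primary success, and the correlations lie in that range. The article contradicts none of these and confirms none. Independently of them, the stated power has no bearing on the clinical and loading domains.

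**What to change.** 1. Name one sagittal-plane gait variable, expressed as an inter-limb difference, as the single primary outcome, tested at two-sided 0.05. The sponsor has to say which variable drove the sample size, because that section cites several and names no joint. It should also state the effect-size metric and any correlation used, since a plain two-sided t-test with d = 0.6 has power 0.71 at 72.
2. Name one primary visit. The first post-training test is preferable because it lies closest to the intervention. The article also has aims reaching to 2 years, so a later visit is possible if it is justified.
3. If claims are wanted in the other two domains, name one lead clinical and one lead loading measure. Test them only if the primary is significant, in a fixed sequence at 0.05 or by Holm (0.05 / 2 = 0.025 for the smaller p-value, then 0.05).
4. Label all other variables and visits secondary, with confidence intervals and no confirmatory claim.

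The change is one of wording and should be dated before groups A and B are unmasked. Treatment, visits and data collection stay as they are. The downside is that most variables now called primary become secondary.

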#### Joint loading

Electromyography (EMG)-driven musculoskeletal modeling will be used to estimate muscle forces from EMG muscle data during walking trials [51]. Anatomical modeling of the pelvis and lower limbs will be scaled initially for each subject. The model will then be calibrated based on muscle parameters used to determine the EMG-to-force relationship. Through iterative adjustments, the muscle parameters will result in strong agreement with the sagittal plane net moments calculated from forward and inverse dynamics. Once the ideal model is determined, the muscle forces will be predicted from mathematical calculations from recorded EMG for three walking trials and converted to muscle force. A frontal plane moment balancing algorithm [52] will be used to calculate medial and lateral compartment contact forces. The knee adduction moment will be calculated using inverse dynamics and will be expressed about each contact point in the medial and lateral compartments. A balance of contact forces and muscle forces at each contact point will be summated to express the contact forces in the each compartment as well as the total joint forces.

### Secondary outcome measures

Return to sport rates, re-injury rates and return to pre-injury level of activity rates will be evaluated 1 and 2 years after surgery. Electromyography measures will be collected simultaneously with gait variables and will be used to further analyze muscle timing, co-contraction and activation patterns before and after the intervention as well as 1 and 2 years after surgery. IKDC 2000, Tampa Scale of Kinesiophobia (TSK-11), Knee Injury and Osteoarthritis Outcome Score (KOOS) including all 5 subsets and the Marx Activity Rating Scale (MARS) are additional patient reported outcome measures that will be collected at all-time points.

### Sample size

Minimal clinically importance differences (MCID) for sagittal plane gait variables have previously been established [18]. A power analysis with β = 0.20, α = 0.05 and a medium effect size (0.3) determined that 72 subjects would be needed to detect differences between groups based on MCID’s. To account for a 10% patient drop out a total of 80 subjects will be enrolled in this study. Forty patients will be in each group dichotomized by gender.

### Data and statistical analysis

Differences between groups will be analyzed using an analysis of covariance (ANCOVA) for biomechanical gait measures and an analysis of variance (ANOVA) will be used for clinical variables. Group assignment will be blinded to the researcher using A and B variables. Assumptions of ANOVA testing will be confirmed prior to statistical analysis. Training group randomization will be used as the between-subjects factor with a within-subjects factor of time. A significance level of p < 0.05 will be set a priori.

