### Interventions

Treatment will be completed at the University of Delaware Physical Therapy clinic by the licensed staff therapists. The therapists have an average of 6.5 yrs experience (range 1 – 20 yrs). All therapists will participate in a training session involving discussion of the treatment program and how to manage changes in effusion, complaints of muscle soreness and still effectively complete the training program. A detailed protocol with visual aids and descriptions will be provided. Once training has been initiated procedural reliability will be completed by an unblinded investigator to ensure that the intervention is properly executed. An unmasked physical therapy clinic liaison will utilize a procedural reliability check list to review three treatment sessions for the first five subjects in each arm of the study. After that each subject’s chart will be reviewed once (Additional file 1). Procedural reliability less than 85% will result in contacting the treating therapist to remedy the situation. Any additional questions regarding the training program will be intercepted by the clinic liaison to ensure blinding of those responsible for data collection is maintained.

The training protocol consists of 10 training sessions with treatment delivered by a licensed physical therapist, regardless of group allocation. Biomechanical and functional data will be collected prior to initiation of the 10 training sessions, after completion of the sessions, and 1 and 2 years after surgery. The training program consists of a series of “prevention exercises”, quadriceps strengthening exercises, agility drills and either PERT training for individuals in the perturbation group or a control exercise for individuals in the STND care group. Details of these exercises are explained in further detail below.

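### The clinical primary outcomes are assigned an ANOVA with no baseline covariate, which costs precision that baseline-adjusted ANCOVA would recover from data already collected

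*Protocol article*

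**What the plan says.** Under Data and statistical analysis, the article splits the methods by type of outcome. For gait, "Differences between groups will be analyzed using an analysis of covariance (ANCOVA) for biomechanical gait measures". For the rest, "an analysis of variance (ANOVA) will be used for clinical variables". The model is then described: "Training group randomization will be used as the between-subjects factor with a within-subjects factor of time". The levels of time are not listed, and the article does not say whether the group main effect or the group by time interaction is the test of treatment.

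The clinical variables matter because, under Outcomes measures, "The primary outcome variables of interest for this study will include gait biomechanics, clinical outcome measures and knee joint loading".

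Baseline values are available. Under Procedure, "Enrolled study participants will complete initial baseline testing and 10 treatment sessions followed by post-training, 1 year and 2 year follow-up testing sessions". Under Interventions, "Biomechanical and functional data will be collected prior to initiation of the 10 training sessions". Under Secondary outcome measures, the additional patient-reported scales are taken at every time point.

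**The concern.** Naming a covariate method for gait and a plain ANOVA for clinical variables in the same sentence is a stated model choice, not a detail left for later. In a randomised comparison with a baseline measurement, adjusting the follow-up value for baseline is, apart from the degree of freedom it uses, at least as precise as comparing changes or comparing follow-up values alone. With about 36 analysable patients per arm, the difference is large enough to notice. What is at stake is the width of the confidence intervals and the chance of detecting a real effect on quadriceps index, hop tests and the patient-reported scores.

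**Working it through.** **Inputs from the document.** Four test occasions: baseline, post-training, 1 year and 2 years (Procedure). 80 enrolled, 40 per group, 10% dropout (Sample size), so 40 × 0.9 = 36 per arm.

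**Inputs assumed.** The correlation r between baseline and follow-up is not given, so 0.3, 0.5 and 0.7 are shown. The standardised difference d is also not given for clinical variables. The Sample size section gives an effect size of 0.3 and calls it medium. Reading that as Cohen's f with two equal groups gives d = 2 × 0.3 = 0.6, borrowed here from gait for illustration. Further assumptions are equal variances at each visit (set to 1), equal correlation between all visits, and two-sided alpha of 0.05.

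**The plan's own figure.** "A power analysis with β = 0.20, α = 0.05 and a medium effect size (0.3) determined that 72 subjects would be needed". With d = 0.6, a two-sample t-test needs 72 in total if alpha is one-sided and 90 if it is two-sided. A two-sided repeated-measures between-group calculation with f = 0.3 also gives 72, with two visits at r = 0.6 or three visits at r = 0.7. Then 72/0.9 = 80, which matches. The figure can be reached, but only with inputs that the article does not state. Nothing below depends on it.

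**Reading A: baseline is a level of time, one follow-up.** Per-patient variances:

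- ANCOVA: 1 − r²
- Group by time, which is the change score: 2(1 − r)
- Ratio: 2(1 − r)/(1 − r²) = 2/(1 + r)

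Power is Φ(d/√(2v/36) − 1.96), where v is the variance above. At r = 0.5, for example, ANCOVA has v = 0.75, so 0.6/√(1.5/36) = 2.94 and power is Φ(0.98) = 0.84. For change, v = 1, so 0.6/√(2/36) = 2.55 and power is Φ(0.59) = 0.72.

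| | r = 0.3 | r = 0.5 | r = 0.7 |
|---|---|---|---|
| Variance, change relative to ANCOVA | 1.54 | 1.33 | 1.18 |
| Power, ANCOVA | 0.76 | 0.84 | 0.95 |
| Power, group by time | 0.58 | 0.72 | 0.91 |
| Total N for 80% power, ANCOVA | 80 | 66 | 46 |
| Total N for 80% power, group by time | 124 | 88 | 54 |

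**Reading A, if the group main effect were the treatment test.** It averages in a visit where the expected difference is zero. With T visits and a constant effect afterwards, the effect becomes d(T − 1)/T: 0.6 × 1/2 = 0.30 with two visits and 0.6 × 3/4 = 0.45 with four. The variance is (1 + (T − 1)r)/T. At r = 0.5, power is 0.31 with two visits and 0.68 with four.

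**Reading A, all four visits, effect constant over three follow-ups.** At r = 0.3, 0.5 and 0.7, ANCOVA on the follow-up mean has power 0.97, 0.98 and 0.995. The three-degree-of-freedom group by time test has 0.58, 0.74 and 0.93.

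**Reading B: time covers follow-up visits only.** Baseline does not enter. With one follow-up the variance is 1 against 1 − r², a ratio of 1/0.91 = 1.10, 1/0.75 = 1.33 and 1/0.51 = 1.96. Power is 0.72 whatever r is, against 0.76, 0.84 and 0.95 for ANCOVA.

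**The case against.** The strongest reply is that the planned model is a standard one, is valid under randomisation, and loses little when r is high (0.91 against 0.95 at r = 0.7). That is correct, and it limits the point to precision. It does not remove the point, because the loss at moderate r is material and avoidable.

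Several stronger readings are tempting but not supported:

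- *Baseline is discarded.* Not if baseline is a level of time, since the interaction then uses it, only inefficiently. It is unused only under Reading B. The article settles neither reading.
- *The effect is diluted.* Only if the group main effect is the treatment test. In a group by time layout the interaction is the usual one, and it is not diluted. The power of 0.31 is therefore not a consequence of the plan as written.
- *Chance baseline imbalance is left in.* Not in the interaction test, which subtracts baseline and tends to over-correct. With 36 per arm, a one-standard-error imbalance is √(2/36) = 0.24 SD. At r = 0.5 it would move the change estimate by −(1 − 0.5) × 0.24 = −0.12 SD.
- *The trial already misses 80% power.* Not established. The 72 can be reproduced under unstated inputs, and the calculation concerns gait variables, for which ANCOVA is planned.
- *Baseline quadriceps index must be a strong predictor because it decides who does strengthening.* This does not follow. The rule is the same in both arms, entry requires at least 80%, and extra strengthening for weaker patients could lower the correlation.

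Two limits also stand. The article does not name the gait covariate, but an article may leave that to the full protocol, so it is not held against the plan. And not every clinical measure clearly has a baseline: the fear scale (ACL-RSI) is described for 6 months to 2 years, while enrolment can start 12 weeks after surgery.

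**Conclusion.** The point holds as a matter of efficiency. For primary clinical outcomes with a baseline value, the stated ANOVA is less precise than baseline-adjusted ANCOVA under either reading of the time factor. On the natural reading with one follow-up, the variance is inflated by 18% to 54% over r = 0.7 to 0.3. In the illustration, power falls by 0.18, 0.12 and 0.04 at r = 0.3, 0.5 and 0.7. The variance ratio rests on equal variances and the assumed r. The power figures also rest on d = 0.6, 36 per arm and two-sided 0.05. That baseline is a level of time is an inference. Validity is not in question, so this is a change that should be made rather than one that must be.

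**What to change.** For each continuous clinical outcome measured at baseline, analyse the post-baseline values by ANCOVA, or by a mixed model over the follow-up visits, with the baseline value of the same measure as covariate. Remove baseline from the time factor. State that the adjusted group difference is the treatment contrast, and at which visit or over which visits it is taken.

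The cost is a short change of wording and about one degree of freedom per model. No new data are needed.
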